#### Secondary outcomes

Secondary outcomes are collected from patients’ records at 12 months after the end of the transition period for each cluster (intention-to-treat analysis) and at 12 months after start intervention for the individual patient defined as the first outpatient clinic visit after the kick-off meeting has been performed (per-protocol analysis). For the secondary outcomes, data will be analyzed and reported using standard descriptive statistics. Mixed-effects regression analyses will be performed where appropriate. For the secondary endpoints, a two-sided alpha < 0.05 will be considered statistically significant. Effect estimates are presented with 95% confidence intervals.

#### Subgroup and sensitivity analyses

Predefined subgroup analyses will be performed to investigate differences between subgroups for the co-primary and secondary endpoints. Subgroup analyses will be performed based on disease duration, hospital volume, pain severity at baseline, QoL at baseline, and disease etiology. A sensitivity analysis will be performed to evaluate the correlation between success of implementation of the intervention and change in the co-primary endpoint.

#### Economic evaluation

The economic evaluation comprises a cost-effectiveness analysis (CEA) and a cost-utility analysis (CUA). The cost analysis is set up from a healthcare and societal perspective. Three cost categories are analyzed, i.e., healthcare costs (Medical Consumption Questionnaire, MCQ), patient and family costs (Medical Consumption Questionnaire, MCQ), and costs from a societal perspective (Productivity Costs Questionnaire, PCQ). For the cost-utility analysis, costs per additional quality-adjusted life years (QALY) are measured by using the EQ-5D “health utility measure”.

#### Safety and interim analyses

There will be no additional risks for patients participating in this trial. The effectiveness and safety of each intervention separately were previously studied and therefore included in current guidelines. There will be no interim analyses performed for safety and treatment effect. An interim administrative look will be performed to monitor recruitment and retention rate. After 5 months of inclusion, the total number of inclusions will be evaluated. If less than 75% of the sample size is reached at that time, the duration of time between each step will be prolonged for the remaining part of the study to maintain the power of > 90%. More details on strategies for achieving adequate participant enrollment are provided in Additional file 1: Supplementary Appendix 1.

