**Fig. 2 Fig2:**
[figure not shown]
Stepped-wedge design with 6 cluster groups. No cluster groups receive the intervention at baseline (6 months); all cluster groups start with continuing current practice. Cluster groups are randomly assigned to unidirectional cross-over to receive the intervention at 2-month intervals. Total trial duration will be a maximum of 35 months; a baseline period of 6 months, a current practice period of varying in length, a transition period of 1 month, an intervention period of 12 months, and a follow-up period with a minimum duration of 6 months for those patients participating in the per-protocol analysis

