### Sample size calculation

Sample size calculation is performed for the primary analysis population and is based on detecting the minimal clinically relevant difference (target difference) in the average PANQOLI scores and the Izbicki pain scores between the two study groups (current practice versus intervention). The protocol committee agreed by consensus on a clinically relevant difference of 10 points on the Izbicki pain score on average. Based on previously performed studies, we assumed a mean difference of 10% in QoL scores [22–24].

No high-quality data on the dynamics of PANQOLI scores have been reported yet; therefore, the Physical Component Summery scores of the SF36 (SF36_PCS) are used for simulations as being the best proxy. The intervention is considered successful if either or both pain and QoL scores improve. Therefore, to adjust for multiple testing, a two-sided alpha of 0.025 is used. We used data from the CARE registry to calculate our sample size [19]. The Izbicki pain score required a larger sample size as compared to SF36_PCS. This is mainly due to a larger within-patient variability of both intercept and slope. The model and parameters we used to determine the intra-patient variability and random error for the Izbicki pain score and to calculate the sample size are provided in Additional file 1: Supplementary Appendix 5. Based on this design, with 120 subjects the power to demonstrate an average slope change of 10 points reduction after 365 days is > 90%.

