#### Primary and secondary analysis populations

In this study, all CP patients who meet the inclusion criteria, regardless of their time since diagnosis, are eligible for participation. However, the primary analysis study population consists of patients with a time since diagnosis ≤ 3 years at the start of the intervention. This population is chosen since in these patients the intervention is intended to start early after diagnosis and the investigators postulate that the impact of the intervention may depend on the time since diagnosis. Secondary analysis populations include patients with a time since diagnosis between 4 and 10 years and > 10 years and the total population.

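### The month-5 recruitment rule counts all inclusions against a sample size set only for patients within 3 years of diagnosis, so meeting it does not by itself protect the stated power

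*Protocol article*

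**What the plan says.** All statements are in the protocol article.

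- **Sample size calculation:** "Sample size calculation is performed for the primary analysis population". The result is "with 120 subjects the power to demonstrate an average slope change of 10 points reduction after 365 days is > 90" per cent, and "a two-sided alpha of 0.025 is used" for each co-primary endpoint.
- **Primary and secondary analysis populations:** the primary population is limited to patients at most 3 years from diagnosis when the intervention starts. Patients who meet the inclusion criteria, "regardless of their time since diagnosis, are eligible for participation".
- **Safety and interim analyses:** the check is "After 5 months of inclusion, the total number of inclusions will be evaluated". The condition for acting on it is "If less than 75% of the sample size is reached at that time", and the planned action is that "the duration of time between each step will be prolonged for the remaining part of the study to maintain the power of > 90" per cent.
- **Fig. 2 caption:** "Total trial duration will be a maximum of 35 months". Study design and setting also gives 35 months, and asks that every cluster deliver the intervention for at least 18 months.
- **Trial status:** 521 patients included, not split by time since diagnosis. Publication was held back until all clusters had crossed over.

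**The concern.** The rule puts one population in the numerator and another in the denominator. The numerator is everyone enrolled. The denominator, 120, is the number of recently diagnosed patients that the primary analysis needs. The power that the rule is meant to maintain is the power of that primary analysis, to which patients with longer disease contribute nothing. The two counts agree only if every included patient is within 3 years of diagnosis, and the eligibility criteria do not require that.

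At stake is a decision rule that could report adequate recruitment when the group that matters is behind, and so leave its own remedy unused. The same ambiguity affects the figure of 521: without a split by disease duration, a reader cannot tell whether the primary analysis has its 120 patients.

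A second, smaller question is whether the remedy of longer steps fits the duration limits stated elsewhere in the article.

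**Working it through.** **Inputs from the article.** Sample size 120 and power above 90% at two-sided alpha 0.025 (Sample size calculation); trigger 75% after 5 months (Safety and interim analyses); 6 clusters, 6-month baseline, 2-month steps, at least 18 months of delivery (Study design and setting); 1-month transition, 12-month intervention, at least 6 months of follow-up, maximum 35 months (Fig. 2 caption); 521 inclusions (Trial status).

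**Assumed input.** The share *s* of inclusions within 3 years of diagnosis at the start of the intervention. The article gives none; 25-50% is used for illustration.

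**1. The plan's own duration.** Baseline + (clusters - 1) x step + transition + intervention + follow-up = 6 + 5 x 2 + 1 + 12 + 6 = 35 months. This matches the stated figure exactly. The stated power cannot be checked in the same way, because its variance parameters are in a supplementary appendix that is not shown. The point does not depend on whether 120 is right, only on whom it refers to.

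**2. The trigger.** 0.75 x 120 = 90 inclusions of any disease duration.

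**3. Primary-population patients when the rule is just met (90 x *s*).**
- *s* = 25%: 22.5, or 19% of 120
- *s* = 50%: 45, or 38% of 120
- *s* = 100%: 90, the intended 75%

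**4. What that checkpoint implies for the end of recruitment.** Patients are recruited during each cluster's current-practice phase. With a 6-month baseline and 2-month steps, these phases last 6, 8, 10, 12, 14 and 16 months, mean 11. Assuming a constant and equal rate per cluster, 90 at month 5 projects to 90 x 11/5 = 198 inclusions. At *s* = 25-50% that is about 50-99 primary-population patients, or 41-83% of 120. On these assumptions a trial that only just met the rule would reach 120 only if *s* were at least 120/198 = 61%.

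**5. What was actually included.** 521 x 0.25 = 130 and 521 x 0.50 = 260. The break-even share is 120/521 = 23%.

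**6. Illustrative power for a final count of n.** Take power as exactly 90% at 120 and information as proportional to the number of patients. Then power = Phi((2.241 + 1.282) x sqrt(n/120) - 2.241).
- n = 60: Phi(3.523 x 0.707 - 2.241) = 60%
- n = 90: Phi(3.523 x 0.866 - 2.241) = 79%
- n = 104 (20% of 521): Phi(3.523 x 0.932 - 2.241) = 85%
- n = 120: 90%

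The article claims more than 90% at 120, and the true model has cluster and repeated-measures structure, so these values only indicate scale.

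**7. Room for longer steps.** With all steps at 3 months and the later periods kept, 6 + 5 x 3 + 1 + 18 = 40 months, 5 over the maximum. Holding 35 months instead leaves 35 - 6 - 15 - 1 = 13 months after transition in the last cluster, against the 18 asked for. Longer steps also postpone the date at which the 3-year limit is judged, so some patients already included could pass out of the primary population.

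**The case against.** The strongest reply is that the mismatch had little consequence here. The month-5 look was a checkpoint and recruitment continued well beyond it, so 23-45 patients is not a projected final sample. Across the whole assumed 25-50% range, the 521 inclusions give at least 130 primary-population patients. The look itself is long past: the first inclusion was on 17 September 2020, and all clusters have since crossed over. The end date of 31 July 2023 lies about 34.5 months after that first inclusion, so the prolongation seems never to have been used. All of this stands, and it limits the point to a rule that is wrong as written and a count that has not been reported.

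Three stronger readings are tempting, and the documents do not support them.
- *That the primary analysis is badly under-filled.* The article gives no split by disease duration, and a shortfall needs a share below about 23%.
- *That this rule is the only safeguard for power.* The same section refers to further enrolment strategies in a supplementary appendix that is not shown.
- *That the article presents 521 as about four times the requirement.* It reports 521 without comparing it with 120 and makes no claim about power from it.

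On duration, it is fair to say that lengthening the steps is an openly declared departure from the planned schedule, and that only the Fig. 2 caption calls 35 months a maximum. With 3-month steps under that cap, 13 months would remain after transition, which still covers the 12-month intention-to-treat endpoint. The conflict is therefore with the stated limits and not necessarily with the primary endpoint.

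None of this makes the rule correct. The article itself states the count, the population and the purpose, and they do not fit together; this is not detail left to another document.

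**Conclusion.** The point holds as a mismatch in a stated decision rule. Meeting the threshold of 90 total inclusions does not show that the primary population is at 75% of its target, and so does not by itself maintain power above 90%. At an assumed share of 25-50%, the threshold is met with 23-45 primary-population patients at month 5.

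Whether the trial ended short cannot be determined from the article. If at least about 23% of the 521 patients were within 3 years of diagnosis when the intervention started, the 120 are there; if the share was lower, power falls gradually, to roughly 85% at a 20% share under the approximation above. The trial may well be adequately powered.

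The timing conflict is minor. The planned schedule uses exactly 35 months, so any prolongation exceeds the stated maximum or cuts into the 18-month minimum, and the article does not say which gives way.

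**What to change.** 1. Reword the rule so that it counts inclusions expected to be at most 3 years from diagnosis at their cluster's cross-over, against 90 of 120. Because cross-over dates are disclosed to centers only as they approach, this projection would have to be made by someone who holds the allocation schedule, such as the independent trial statistician.
2. The month-5 look is past and all clusters have crossed over, so the useful step now is to report how many of the 521 meet the primary-population criterion. If that number is below 120, state the power for it, using the variance model of the original calculation.
3. Reconcile the prolongation clause with the 35-month maximum and the 18-month minimum delivery by stating which limit would yield, or record that the clause was not used.

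The cost is one count in the database and a few sentences. It needs no outcome data and no change in trial conduct. The stated power may turn out less favourable.

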## Discussion

The COMBO trial is the first stepped-wedge cluster-randomized controlled trial designed to determine whether standardization of care through the implementation of an evidence-based algorithm improves clinical outcomes in patients with CP.

Although several interventions have been studied in patients with CP, these were often studied as stand-alone intervention or in selected patients, but not combined as an “integrated management algorithm”. The Dutch multicenter randomized ESCAPE trial compared the effect of early surgery to an endoscopy-first approach on pain in CP patients. In this study, early surgery resulted in significantly less pain over 18 months compared to the step-up approach [20]. Remarkably, this did not lead to an improved QoL. This highlights the need to better understand contributing factors to an impaired QoL in patients with CP [6]. Factors influencing QoL have been extensively investigated in previous studies (e.g., pain pattern and severity, opioid usage, alcoholic etiology, current nicotine and alcohol use, unemployment, EPI, low BMI, bowel symptoms, fear of future, and self-blame) and accounted only for 27 and 18% of the difference in physical and mental health QoL [6, 26–28]. Recently, a mono-center pilot-study has investigated the impact of a dedicated multidisciplinary CP team and has shown promising results in terms of improving QoL and reducing the use of opioids [24]. However, up to now, the impact of an evidence-based algorithm involving multiple domains of disease management on patients’ outcomes has not been evaluated. The COMBO trial will be the first study assessing whether standardization of care through the structured implementation of an evidence-based algorithm improves patient-centered and clinical outcomes in patients with CP and whether it reduces health care and societal costs. This multicenter study is performed on a nationwide level in 26 participating hospitals. The intervention components included in our evidence-based algorithm are based on recommendations stated in society guidelines and therefore we consider them as “state-of-the-art practice” and believe these should be provided to all patients with CP.

By implementing our evidence-based algorithm in clinical practice, we aim to reinforce and improve current clinical care and, subsequently, improve patients’ outcomes. When the intervention (i.e., evidence-based algorithm and its tools) is successfully implemented in all participating centers and provse to be of value in improving QoL and reducing pain severity, it will become the new standard of care for patients with CP.

In the present study, the intervention is implemented in a stepwise manner. Therefore, clusters are randomized instead of individual patients. In the end, the intervention rolls out to all included patients of the participating centers. This study design was chosen for several reasons. First, cluster randomization allows us to measure the impact of our evidence-based algorithm on patients’ outcomes at group level instead of at individual patient level taking into account the complexity of daily care. If individual participants were randomized such as in a traditional randomized controlled trial design, it would be difficult for physicians to avoid contamination, i.e., to not apply in patients randomized to the control group what they learned for the intervention group. Second, we consider our evidence-based algorithm as “best practice” and believe standard CP care should comprise all intervention components of our algorithm. However, for logistical and practical reasons, it is not feasible to introduce the intervention in all participating hospitals at once. By rolling out the intervention in a stepwise manner at cluster level, the intervention will eventually be delivered to all included patients. Furthermore, this stepwise implementation allows to investigate the impact of the intervention over time. For these reasons, we have opted for a stepped-wedge cluster-randomized controlled trial design. One potential drawback of the stepped-wedge design used in this study is the risk of contamination. Introducing this trial in the Netherlands will result in an increased awareness for CP which could possibly lead to higher compliance to the HaPanEU guidelines in the control period. In order to minimize the risk of contamination, the content of the algorithm will only be accessible for local treating physicians in the intervention phase.

In conclusion, the COMBO trial is a stepped-wedge cluster-randomized controlled trial to investigate whether standardization of care by implementing a bundled evidence-based algorithm covering several domains of care improves QoL and pain severity in patients with CP as compared with current practice.

## Trial status

The trial was registered on the 5th of September 2020 in the ISRCTN registry. The first patient was included on the 17th of September 2020. To date, 521 patients have been included in this trial. This trial will run until the 31st of July 2023. The protocol publication has been postponed until all clusters crossed over to the intervention to avoid contamination of the control group.

## Data Availability

Patients are coded by a numeric randomization code (anonymized), based on the chronological order of inclusion. The source data will be centrally collected and stored at the datacenter of the DPSG (St. Antonius Hospital, Nieuwegein) for a minimum of 15 years. The coordinating investigators ([name] and [name]) are responsible for the implementation and coordination of this trial, patient enrollment, data collection, and data analyses. The results of this trial will be verified by an independent statistician. All coauthors will interpret the data and collaborate on the final manuscript preparation. Study results will be published in a peer-reviewed journal.
